## **10. ETHICAL CONSIDERATIONS**

### **10.1. General considerations**

This trial will be conducted according to the Declaration of Helsinki, the Good Clinical Practice guides of the ICH (International Conference of Harmonization), Madaus, S.A.'s SOPs, and Quintiles' and the legislation in force (Royal Decree on clinical trials 223/2004).

### **10.2. Data Confidentiality**

The investigator will guarantee that all the persons involved observe the confidentiality of any information on the trial subjects (Article 37 R.D. 223/2004).

All the parties involved in a clinical trial will observe the strictest confidentiality to ensure that the personal or family privacy of the subjects participating in it is preserved. Similarly, suitable measures should be taken to avoid the access of unauthorised personnel to the trial data (Article 3 R.D. 223/2004).

The treatment of the personal data of the subjects participating in the trial, particularly with regard to consent, will comply with the provisions of the Constitutional Law 5/1992 of 29 October (Article 3 R.D. 223/2004) and European Directive on Data Protection (95/46/EC).

The data obtained in this study will be checked by a monitor appointed by the sponsor and will be used exclusively to draw scientific conclusions. The identity of the patients is confidential and will be known only by the investigator and his collaborators, the auditors and monitors appointed by the sponsor and the inspectors of the competent authorities.

### **10.3. Trial Insurance**

The sponsor, Madaus, S.A., has taken out a public liability insurance policy for a maximum sum of 250.000 € per subject included in the clinical trial (art. 8 RD 223/2004) (Annex 10)

The insurance will cover all the liabilities of the sponsor, the investigators and his collaborators and the proprietor of the Hospital or Centre where the trial is conducted (Art. 8 of the RD 223/2004).

It is assumed, unless proven otherwise, that injuries affecting the health of the person involved in the trial, during the trial and in the period of one year following the end of the treatment, took place as a result of the trial. However, after one year has elapsed the trial subject is required to prove the link between the trial and injury or damage.

#### **10.4. Independent Ethics Committee (IEC)**

Before the study begins, the sponsor and the investigator should obtain the written approval or favourable opinion of the IEC for this protocol, the Informed Consent Form, the material used for patient recruitment (e.g. announcements) as well as any written information provided to the patients. Furthermore, they should provide the IEC with the Investigator's Brochure or Summary of Product Characteristics, the information sheet given to the subject and any update.

Madaus, as sponsor, should send reports, updates and any other information to the IEC (e.g. Safety Reports, Amendments to the Protocol, Administrative Letters) in accordance with the requirements of the regulatory authorities or procedures of the institution ( R.D. 223/2004).

#### **10.5. Informed consent**

The preparation of the Informed Consent Form is the Investigator's responsibility. It must include all the elements required by the ICH, GCP and the applicable regulatory directives, and should comply with Good Clinical Practices and the ethical principles promoted by the Declaration of Helsinki (Annex 9). The consent form should also include a declaration that the sponsor and the health authorities may have direct access to the subjects' records. Before the study begins, the written approval/favourable opinion of the IEC on the Informed Consent Form and any other information provided to the subjects should be obtained.

The subject will preferably give his consent in writing, or else orally before witnesses independent of the investigating team, who will be present during the discussion of the informed consent and will declare on their own responsibility. After the subject has given his oral consent, the witnesses should personally sign and date the Informed Consent Form indicating that the information provided is accurate, and that the subject has understood it and given his consent freely (Annex 4).

The Investigator should provide the subject or his legally authorised representative with a copy of the consent form and of the Patient Information Sheet in a non-technical and easy-to-understand language. The Investigator should give the subject or his legally authorised representative time to ask questions on the details of the study. Then, the subject or his legally authorised representative and the person who participated in the discussion of the informed consent will sign and date the informed consent personally. The subject or his legally authorised representative should receive a copy of the Informed Consent Form and any other written information provided to the subject on the study before participating in the study.

The informed consent and any other information provided to the subject or to his legally authorised representatives should be revised whenever new information becomes available and which is relevant to the voluntary participation of the subject, and should be approved or given the favourable opinion of the IEC before it can be implemented. The Investigator, or the person appointed by him, should inform the subject or his legally authorised representative comprehensively on all the relevant

aspects of the study, and on any new information that may affect the subject's disposition to continue to participate in the study. This communication must be documented.

During the participation of a subject in the trial, any update of the consent form or of the Patient Information Sheet should be provided to the subject.

The subject participating in a clinical trial or his representative may withdraw his consent at any time, without having to account for their decision and without this entailing any liability or prejudice to them (art. 7.5 RD 223/2004).

### **10.6. Confidentiality**

The investigator will guarantee that all the persons involved observe the confidentiality of any information on the trial subjects (Article 3.2 R.D. 223/2004).

All the parties involved in a clinical trial will observe the strictest confidentiality to ensure that the personal or family privacy of the subjects participating in it is preserved. Similarly, suitable measures should be taken to avoid the access of unauthorised personnel to the trial data (art. 3 R.D. 223/2004).

The treatment of the personal data of the subjects participating in the trial, particularly with regard to consent, will comply with the provisions of the Constitutional Law 15/1999 of 13 October (Article 3.2 R.D. 223/2004) and the European Directive on Data Protection (95/46/EC).

The data obtained in this study will be checked by a monitor appointed by the sponsor and will be used exclusively to draw scientific conclusions. The identity of the patients is confidential and will be known only by the investigator and his collaborators, the auditors and monitors appointed by the sponsor and inspectors of the competent authorities.

### **10.7. Trial Budget**

See Annex 15.

### **10.8. Insurance policy**

The Spanish Legislation requires coverage for subjects participating in clinical trials with a public liability policy (Article 8, R.D. 223/2004). The study sponsor, Madaus, has taken out this policy, in accordance with the legislation in force (Annex 10).

## **11. PRACTICAL CONSIDERATIONS**

### **11.1. Responsibilities of all the participants**

#### **11.1.1. Compliance with the protocol and amendments to the protocol**

The study will be carried out as described in this approved protocol. All revisions should be discussed and revised by the investigator and the Coordinator.

Any amendment to an already authorised clinical trial protocol must be reported to the Independent Ethics Committees (IEC) involved in it, to the Spanish Medicines Agency and the Autonomous Communities. When the amendment is relevant, a prior report by the IEC involved in the trial and authorisation by the Spanish Medicines Agency will be required. Relevant amendments will be those that entail an increased risk for the subjects participating (Article 25 R.D. 223/2004).

The investigator may not implement any deviation or change in the protocol without the prior revision and documented approval/favourable opinion by the IEC regarding any such amendment, except for any changes whose purpose is to remove an immediate risk for the study subjects. Any significant deviation from the protocol should be documented in the case report form.

If a deviation or change in the protocol is implemented before the approval/favourable opinion of the IEC is secured, in order to remove an immediate risk, any such deviation/change shall be submitted, as soon as possible, to:

- the IEC for its revision and/or favourable opinion;
- the Spanish Medicines Agency.

The documentation pertaining to the approval signed by the president or the person designated by the latter in the IEC should be sent to the sponsor.

If the revision is an administrative letter, it should be submitted to the IEC, to the Spanish Medicines Agency and to the Autonomous Communities for their information.

If an amendment substantially alters the study design or increases the potential risk for the subject: 1) The Informed Consent form should be revised and be resubmitted to the IEC for revision and approval/favourable opinion; 2) The revised form should be used to obtain the consent of the subjects already included in the study if they are affected by the amendment; 3) the new form should be used to obtain the consent of new subjects before recruitment.

The revised form should also be sent to the Spanish Medicines Agency (Article 25, R.D. 223/2004).

## **11.2. Control of compliance in the protocol**

The sponsor's representatives should be allowed to visit all the study centres periodically to check data integrity and to validate the quality and the veracity of the study. The study documents will be revised at the centre and compared with the original documents, talks will be held with the investigator on the progress of the study and the suitability of the facilities will be assessed constantly.

Furthermore, the study may be evaluated by the sponsor's internal auditors and by the inspectors designated by the Health Authorities, who will be given access to the CRFs, original documents and other study archives. The reports of the audit carried out by the sponsor will always be kept confidential.

The investigator should notify the sponsor quickly of any scheduled audit by any health authority, and promptly send copies of the audit report to the sponsor.

## **11.3. Data filing**

### **11.3.1. Files and reports**

The Investigator should prepare and maintain suitable and accurate records designed to log all the observations and other data relevant to the research in each subject treated with the investigational product or included as a control in the trial.

The investigator will be responsible for ensuring that the data are duly recorded in the electronic Case Report Form for each patient and that they are consistent with the original documents, or in the case of discrepancy an explanation should be provided.

The subjects should be identified by their initials, date of birth and by the patient's number, as applicable. All the information required should be included in the CRF in the spaces provided for this purpose. If a datum is not available or is not applicable, it should be documented as such; no blank spaces should be left.

Each investigator will sign the electronic case report forms in order to ensure that the observations and findings have been recorded fully and accurately. The investigator will maintain a sheet of signatures to document the signatures and initials of all the people authorised to input or correct data in the CRFs.

The confidentiality of any documents that might identify the subjects must be protected, observing their privacy and the rules of confidentiality in accordance with the applicable regulatory requirements.

This protocol will use the software belonging to "Quintiles" and any updates which may be made known during the course of the trial, in order to record data electronically at the study site and to be able to revise the data electronically.

### **11.3.2. File storage**

The sponsor is responsible for the storage of the trial dossier. The investigator will keep the patient identification codes for at least 15 years after the conclusion or interruption of the trial. The clinical records of the patients and other original data will be stored for the maximum period of time allowed by the Hospital, institution or centre where the trial is carried out

The investigator should contact the sponsor before destroying any record associated with the study. The sponsor will notify the Investigator as soon as it is no longer necessary to keep the trial archives.

Should the investigator withdraw from the study (for example, transfer, retirement), the records should be transferred to another person appointed by mutual agreement (for example, another investigator, IEC). Written notification of this transfer should be sent to the sponsor.

### **11.4. Samples for clinical research and labels**

The medication will be provided by the trial sponsor, duly labelled according to the applicable standards.

The pharmacy service, and in exceptional cases the investigator, are responsible for ensuring that an updated Register of the availability of the investigational drug is kept at each Investigation Centre where the investigational product is registered and stored.

The records or notebooks should comply with the applicable regulations and directives and should include:

- Amount received and located in the storage site
- Amount currently stored
- Label ID number or batch number
- Dates and initials of the person responsible for entering and removing drugs from the inventory
- Amount dispensed and returned by each subject, including the subject's unique identifier
- Amount transferred to another area for dispensing or storage
- Use of medication outside the study (e.g. due to losses, wastage, damage)
- Amount returned to the sponsor
- Amount destroyed at the investigation centre, as applicable
- Samples sent to third parties for bioavailability/bioequivalence, as applicable

The sponsor will provide forms to facilitate inventory control if the investigation centre personnel do not have a system fulfilling these requirements in place.

Once the study has been completed or terminated, all unused and/or partially used drugs should be returned to the sponsor if the centre is not authorised to destroy them.

### **11.5. Publication policy**

In order to prevent the premature communication of information and patentable inventions, the publication of the results will be performed by common agreement with all the investigators and the sponsor.

All publications, abstracts, communications at congresses, etc., will be signed by the principal investigator. In the case of multicentre studies, the order of the signatories will depend on the number of patients included at each centre, barring the principal investigator, who will sign first, or the person designated by him to draft the text to be published.

## **12. STATISTICAL ANALYSIS**

### **12.1. Descriptive analysis**

The description of the endpoints studied will be performed according to conventional techniques.

The quantitative endpoints will be described using means, standard deviations, quantiles and outliers, whereas the qualitative endpoints will be described by means of frequency tables.

The normality of the quantitative endpoints will be evaluated by the usual normality tests (Kolmogorov-Smirnoff)

If a normal distribution and homoscedasticity are assumable in the values of an endpoint, parametric analysis procedures will be used in subsequent inferential studies.

Non-normal distribution endpoints will be transformed as necessary to normalise the distribution of their values. If no transformation that meets the premises of normality is found, equivalent non-parametric procedures will be used alternatively in the analysis of this endpoint.

### **12.2 Homogeneity of samples**

For visit S0, a determination will be made to establish whether the patients of both treatment groups are homogeneously distributed in terms of age, gender, lipid profile, mineral plasma levels, vitamin plasma levels, blood test parameters, weight and genetic polymorphisms.

For the quantitative variables, the homogeneity of the samples will be evaluated by the Student's *t* test if the normality premises are met; otherwise the Mann-Whitney non-parametric test will be used. The Chi square test will be used for qualitative endpoints.

In all cases, the null hypothesis considered will be the non-existence of differences between the two treatments for a two-tailed level of significance of 0.050.

### **12.3 Efficacy analysis**

#### **12.3.1 Primary efficacy analysis.**

The primary efficacy analysis will be conducted to evaluate the effect of the treatment with *Plantago ovata* husk versus placebo with regard to plasma LDL-C concentrations in patients with moderate hypercholesterolemia with low saturated fat diet.

The changes in the values of the plasma LDL-C concentrations will be evaluated by creating two endpoints:

- The primary analysis of the primary evaluation will be carried out with the total difference in the concentrations of LDL-C in plasma between visit S8 and visit S0 between both study groups.

- As additional sensitivity measure, the percentage of reduction of the concentrations of LDL-C in plasma between visit S8 and visit S0 between both study groups will also be evaluated.

The principal working hypothesis will be:

$$H_0: \Delta \text{LDL } \textit{plantago ovata} - \Delta \text{LDL placebo} < |7.5| \text{ mg/dl}$$

$$H_1: \Delta \text{LDL } \textit{plantago ovata} - \Delta \text{LDL placebo} \geq |7.5| \text{ mg/dl}$$

Where  $\Delta \text{LDL}$  = final LDL – baseline LDL

The statistical analysis will be carried out using a covariance analysis (ANCOVA) model with the baseline value as co-variable:

$$Y_{it} = \mu + Y_{it\text{BASELINE}} + T_t + e_{it}$$

where,

- |                         |                                                                                                                                              |
|-------------------------|----------------------------------------------------------------------------------------------------------------------------------------------|
| $Y_{it}$                | indicates the value of variable Y (difference in concentrations between visit S8 and visit S0) measured for patient I receiving treatment T. |
| $Y_{it\text{BASELINE}}$ | indicates the baseline value of the variable Y (difference in concentrations between visit S8 and visit S0) measured for patient I.          |
| $\mu$                   | indicates the overall average                                                                                                                |
| $T_t$                   | indicates the fixed effect of the treatment (T = 1 a 2)                                                                                      |
| $e_{it}$                | indicates residual error, where $e_{it} \sim N(0, \sigma_e^2)$                                                                               |

In order to study other variables at other post-baseline visits, when necessary, an ANCOVA model will be made for each one, analogous to that described above. The baseline homogeneity will be evaluated using a Student's *t* test for independent data.

The variation in the LDL-C concentrations for week 8 to week 16, will be measured by way of intragroup analysis using analysis methods for repeat measurements.

The level of statistical significance will be established at 0.05 bilateral.

The evaluation of the continuous secondary efficacy endpoints will be analogous with the previously described ANCOVA for the primary endpoint. The continuous secondary endpoints to be analysed are described below:

- Weight and blood pressure
- Total cholesterol, triglycerides, HDL cholesterol, apolipoproteins (apo) B-100 and A-1 and lipoprotein (a).
- The oxidation markers: alpha tocopherol and gamma tocopherol in LDL, resistance of LDL to oxidation (lag time), LDL oxidation "in vivo" and lipid lipoperoxides.
- The inflammation markers: IL-1beta, interleukin-6, TNF-alpha, amyloid-A, high sensitivity C-reactive protein, fibrinogen, leukocytes.

- The indicators of antithrombotic activity: folic acid, homocysteine, plasminogen activator inhibitor (PAI-1).
- The individual response to the plasma lipids and their modulation by apolipoprotein E polymorphisms, cholesterol ester transport protein (CETP), apolipoprotein A-V, FABP 2, ABCG5 and ABCG8, fibrinogen, fibrinogen activator inhibitor, angiotensin converting enzyme and other polymorphisms which might describe their involvement in the development of cardiovascular diseases.
- Fasting complement component 3 (C3)
- Mannose-binding lectin (MBL) activity
- Remnant-like particle cholesterol concentration (RLP-C)
- Parameters of cholesterol absorption and synthesis: plant sterols (campesterol and beta-sitosterol, reflecting cholesterol absorption) and lathosterol (reflecting cholesterol synthesis)
- Determination of atherogenic apo B-containing particles (VLDL, IDL and LDL subclasses),
- HDL particle phenotype and HDL particle composition
- Cholesterol ester transfer protein activity

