### **5.2. Detailed description of the randomisation process**

The eligible subjects will be randomly assigned to treatment A or B in a ratio of 1:1. With the aim of minimising potential bias in the result of this study because of the subjects, investigators or study personnel, in relation to the safety, efficacy or well-being of the study products, the study design will be double-blind. The subjects will be randomly assigned to treatment in a ratio of 1:1; the probability of any subject receiving either of the two treatments described for this study will therefore be 0.5.

The investigator or the study personnel will include subjects suitable to participate in the study sequentially by number of subject and centre, starting with the first patient and centre number of the numerical series assigned by MADAUS. The sponsor responsible for the randomisation will guarantee the randomisation code. The authorised personnel will provide the randomisation code.

The randomisation list consists of 09 centres, each centre containing 25 blocks of 4 patients per block; the final list being of 999 patients. This list has been programmed by Quintiles Trans. Version 8.2 of the SAS statistical package has been used.

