### 6.3. Sample size

#### Total sample: 290 patients (145 per group)

The results of an earlier study by Sprecher 1993, measuring the effect of 10.2 g of *Plantago ovata* a day in the reduction of the levels of LDL cholesterol were used to calculate the sample.

The value of the effect to be detected ( $d = 7.5$  mg/dl) is equivalent to a reduction of 5% of LDL in patients with LDL baseline values of 150 mg/dl.

The working hypothesis is:

$$H_0: \Delta \text{LDL } \textit{plantago ovata} - \Delta \text{LDL placebo} < |7.5| \text{ mg/dl}$$

$$H_1: \Delta \text{LDL } \textit{plantago ovata} - \Delta \text{LDL placebo} \geq |7.5| \text{ mg/dl}$$

Where  $\Delta \text{LDL} = \text{final LDL} - \text{baseline LDL}$

For a statistical significance of  $\alpha = 0.05$  and a power of 80%, with a standard deviation of 20 mg/dl in the  $\Delta \text{LDL}$ , the sample size required to detect significant differences of 7.5 mg/dl between the group treated with *Plantago ovata* and the group treated with placebo is 112 patients per group, for which, adjusted to an expected percentage of losses of 15%, a total of **270 patients** will be required.

After treatment, approximately 75% of the patients treated with soluble fibre (84 patients) and 85% of those treated with placebo (95) will not have 130 mg/dl of LDL-C in plasma. A statin will be added to all these patients' treatment.

It is assumed that the combination of soluble fibre with statins will cause the mean value of LDL-C to fall from 157 mg/dl to 125.6 mg/dl ( $\Delta \text{LDL}$  soluble fibre + statin = 31.4 mg/dl). In the placebo + statin group from 161 mg/dl to 136.85 mg/dl ( $\Delta \text{LDL}$  placebo+statin = 24.15 mg/dl).

For a statistical significance of ( $\alpha=0.05$ ), a power of 80%, a standard deviation in the  $\Delta \text{LDL}$  of 18.5 mg/dL and a ratio of 0.85 between groups treated with placebo for 0.75 treated with soluble fibre, **the sample size** necessary to detect differences of

7.25 mg/dl in the  $\Delta$ LDL between the group treated with statin+soluble fibre and the group treated with statin + placebo is 111 patients in the placebo group and 98 patients in the soluble fibre group.

As the percentage of failure in the objective of LDL-C equal to or lower than 130 mg/dl is 75% in the patients treated with soluble fibre and 85% in those treated with placebo, adding a 10% of patients lost to follow-up means that a **total sample of 290 patients (145 per group)** will be required.

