## **12.4. Analysis populations**

The statistical analysis will be performed both for intention to treat (each patient is analysed in the group he/she was assigned to at the beginning of the study regardless of whether he/she did not comply with the corresponding intervention) and by protocol, which only includes patients who complied suitably with the intervention that was assigned to them.

The safety analysis will include all the patients who received study medication; the adverse events in each treatment will be described graphically and/or numerically.

The Spanish version 11 of the statistical application package SPSS will be used for the data analysis.

A two-tailed significance of 0.05 will be considered in all statistical tests.

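### The primary hypotheses put the null boundary at 7.5 mg/dl, but the sample size and the planned ANCOVA correspond to a null of zero, and the written sign conflicts with the definition of ΔLDL

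*Protocol*

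**What the plan says.** Protocol 6.3 and 12.3.1 give the same pair of hypotheses. The null is that ΔLDL on Plantago minus ΔLDL on placebo is below |7.5| mg/dl. The alternative is that it is at least |7.5| mg/dl: "\Delta \text{LDL placebo} \geq |7.5" in the formula of 12.3.1, where the pair is called the principal working hypothesis. ΔLDL is defined as "final LDL – baseline LDL".

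Section 6.3 uses the same number as the effect to be found: "the sample size required to detect significant differences of 7.5 mg/dl between the group treated with" the Plantago and placebo arms. It explains that 7.5 mg/dl "is equivalent to a reduction of 5% of LDL in patients with LDL baseline values of 150 mg/dl". The other planning inputs are α = 0.05 "and a power of 80%, with a standard deviation of 20 mg/dl in the" change, which leads to 112 patients per group. The final total of 290 (145 per group) comes from the later statin-phase calculation.

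The primary analysis in 12.3.1 is an ANCOVA with a fixed treatment effect and a baseline covariate. No shifted null value and no confidence-limit rule is given. The level is two-sided: "The level of statistical significance will be established at 0.05 bilateral" in 12.3.1, and "A two-tailed significance of 0.05 will be considered in all statistical tests" in 12.4 (Analysis populations).

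The primary objective in 4.2 is worded as the capacity to lower LDL-C by 5%.

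**The concern.** A null that contains every difference up to 7.5 mg/dl belongs to a test of superiority by a margin. A trial planned on a true effect of 7.5 mg/dl then sits on the boundary of its own null, where rejection happens only at the error rate of the test. The sample size and the ANCOVA belong to a different test, that of no difference. The protocol therefore gives two incompatible definitions of success on its primary endpoint.

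The plausible results are the ones affected. An estimate near the planned effect would be significant against zero and would fail against the margin. If the choice between the two is left until the data are seen, it becomes post hoc. If zero is tested and rejected, the written claim of at least 7.5 mg/dl still has no support.

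The sign adds a second contradiction. With change defined as final minus baseline, a benefit makes the difference negative, while |7.5| is simply +7.5.

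**Working it through.** **Inputs.** Difference 7.5 mg/dl, SD of ΔLDL 20 mg/dl, power 80%, 112 per group, 15% losses and 145 per group in the final sample (all 6.3); two-sided α = 0.05 (12.3.1, 12.4); 1:1 allocation (5.2).

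**Step 1: reproduce the plan's figure.** For a test against zero,

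n = 2 × (20/7.5)² × (1.96 + 0.8416)² = 111.6, so 112 per group.

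This matches exactly. A one-sided 0.05 test would give 88. The 112 is therefore the size for a two-sided test of no difference.

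**Step 2: standard errors.** SE = 20 × √(2/n). The group size of 123 is 145 × 0.85.

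**Step 3: both tests at a true benefit of 7.5 mg/dl.**
- Against zero: power = Φ(7.5/SE − 1.96), and rejection needs an observed benefit above 1.96 × SE.
- Against the margin, sign corrected: power = Φ((7.5 − 7.5)/SE − 1.96) = Φ(−1.96) = 2.5% at every n, and rejection needs an observed benefit above 7.5 + 1.96 × SE.

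| n per group | SE (mg/dl) | Power against zero | Observed benefit needed, zero | Power against margin | Observed benefit needed, margin | True benefit for 80% against margin |
|---|---|---|---|---|---|---|
| 112 | 2.67 | 80.1% | 5.2 | 2.5% | 12.7 | 15.0 |
| 123 | 2.55 | 83.7% | 5.0 | 2.5% | 12.5 | 14.6 |
| 145 (no losses) | 2.35 | 89.1% | 4.6 | 2.5% | 12.1 | 14.1 |

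The last column is 7.5 + (1.96 + 0.8416) × SE.

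**Step 4: where the readings disagree.** An observed benefit between the two thresholds (5.2 to 12.7 mg/dl at 112 per group, 4.6 to 12.1 at 145) succeeds against zero and fails against the margin. At a true effect of 7.5 mg/dl the chance of landing there is 80.1 − 2.5 = 77.6% at 112 per group and 89.1 − 2.5 = 86.6% at 145.

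**Step 5: the sign.** Under final minus baseline, the planned benefit is a difference of −7.5. Tested literally against +7.5 with 112 per group, the rejection probability is Φ(−15/2.67 − 1.96), about 2 × 10⁻¹⁴. However, 6.3 itself reports falls as positive ΔLDL: 157 − 125.6 = 31.4 for fibre plus statin, 161 − 136.85 = 24.15 for placebo plus statin, and their difference 7.25 as the benefit. The two sign conventions sit in the same section.

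**The case against.** The best defence is that nobody would run a margin test from this protocol. The ANCOVA in 12.3.1 has no shifted null, the level is two-sided, and 6.3 speaks of detecting a difference of 7.5 mg/dl. Run in the usual way, the treatment term is tested against zero with the intended power, and the estimate and its confidence interval are the same whichever hypothesis is printed. All of this stands. A reader might infer from the hypotheses that the trial's power is only 2.5%; the documents do not support that, because this figure applies only if the written margin is tested with its sign corrected.

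A reader might also infer that the alternative is meant to show Plantago raising LDL-C. The documents do not support that either. The objective is a reduction, the bars around 7.5 suggest a magnitude, and 6.3 elsewhere counts falls as positive. It is a contradiction in notation. Reading the bars as belonging around the difference would cure the sign and leave the margin in place.

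The defence does not remove the contradiction over what counts as success. The margin pair is printed twice, once as the principal hypothesis, and the 5% objective in 4.2 makes a margin claim a plausible reading. Where the protocol wants a null of no difference, it says so: in 12.2 for baseline homogeneity and in 12.3.2 for the success proportions. Nothing in 12.3.1 does this for LDL-C.

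**Conclusion.** The point holds as a contradiction in the stated hypotheses. The number of patients is consistent with a test against zero, and the wording of the null and alternative is the likely defect. It should be fixed because it decides what counts as primary success. At the planned effect, roughly 78% to 87% of trials would give a result on which the two readings disagree.

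The figures assume an SD of 20 mg/dl for the change, with no gain from baseline adjustment, a normal approximation, and two-sided 0.05 taken as 2.5% in the favourable direction. A one-sided 0.05 margin test would give 5% in place of 2.5%. The 89% assumes all 145 per group are evaluable; with the plan's own 15% losses it is about 84%.

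**What to change.** - In 6.3 and 12.3.1, state H0: mean ΔLDL(Plantago) − mean ΔLDL(placebo) = 0 against H1: ≠ 0, two-sided 0.05.
- Name −7.5 mg/dl only as the planning effect, and use one sign convention for ΔLDL throughout, including the statin-phase figures in 6.3.
- Report the adjusted difference with its 95% confidence interval and read it against 7.5 mg/dl for relevance.
- Align the objective in 4.2, so that 5% is the reduction of interest and not something proven by rejecting zero.

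The cost is a few lines in three sections, with no change to data, visits or sample size.

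If superiority by more than 7.5 mg/dl is truly intended, write the margin as −7.5 and restate the power, because the present size does not give 80% for that test at the planned effect. For orientation, 80% power against the margin needs 112 per group if the true benefit is 15 mg/dl, 252 if it is 12.5 and 1005 if it is 10; these true benefits are assumptions, not figures from the protocol. Either choice should be fixed before unblinding.
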